### Health-related quality of life

2.7

Health-related quality of life will be assessed in the standardized questionnaire SF-36. The questionnaire version has been translated into the Czech language.^[21]^ Normative representative study validity, reliability, sensitivity, and task complexity for the European population has been proven.^[22]^ SF-36 was chosen in our study as an assessment tool for its full usability, functional coherence, and high responsibility in repeated testing. It is very often used in studies focusing on CR.^[23]^

### Training adherence and adverse events

2.8

Training adherence and incidence of the adverse events will be recorded in the exercise datasheets from the telemonitoring platform for both groups during the 12-weeks training program.

According to the number of completed training sessions, training adherence will be evaluated through the Polar Flow web application as the overall completion rate of prescribed exercise lessons (100% = 36). The training diary in the web application will provide information about the total average time of all exercises in the defined HR zone and the total number of compliant participants (the criterion of compliance with the rehabilitation program is set at 70% of the prescribed training sections). According to the data obtained, investigators will assess the total training program completion.

The study participants will be encouraged to use the contact details for reporting the incidence of treatment-emergent adverse events at any time throughout the study period. The scale will assess the type, incidence, and severity of adverse events (grade 1: mild, asymptomatic or mild symptoms; grade 2: moderate, minimal; grade 3: severe or medically significant; grade 4: life-threatening consequences; and grade 5: death) will be noted.

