### Study design

2.1

This study is designed as a monocentral randomized controlled trial at University Hospital (UH) Brno in the Czech Republic. All participants provided written informed consent before entering the study. Study data will be collected at baseline (T0), after 3 months (T1), and after 12 months (T2). (Fig. 1) The Institutional Ethics committee approved the study protocol of the UH Brno, Czech Republic. The trial is registered as recommended by the World Health Organization at ClinicalTrials.gov with number NCT04552652. Study data will be password-protected, and only the designated investigator of the research team can access it. The participants’ data will be processed and backed up following the current European General Data Protection Regulations.

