**Figure 2 F2:**
[figure not shown]
Home-based telerehabilitation scheme. The figure represents home-based physical training via telemonitoring and remote guidance. Icons illustrate cardiac telerehabilitation form. The differences in training prescription between the two study groups are shown in the diagram at the top left.

One to 3 pilot training sessions in the outpatient CR center under the supervision of a physiotherapist will undertake all participants before the telerehabilitation program. These pilot sessions’ objective is to educate and practice how to use a wearable HR sensor (Polar H10). As a part of the education, the patients learn how to adhere to the prescribed duration of the physical training and intensity by checking the correct HR zone. Further on, the patients will be instructed about preferred training modality in a home-based environment (cycling, walking, or Nordic walking) and receive advice on how to perform the modality. Subsequently, the patients will be educated on how to use the HR sensor correctly and upload the training data to the web application (Polar Flow).

Throughout the study, the patients will be able to check training data and results to see if they are meeting their training goals. The personal coach (physiotherapist) will be able to view the data in the application and also provide remote guidance (motivation, feedback on the frequency, duration, and intensity of training) via a preferred phone call once a week (Fig. 2). After 3 months, the telemonitored training sessions will be completed. Patients will be recommended to keep on doing exercises with the HR sensor and web application. A long-term effect will be assessed in a 1-year follow-up.

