### Outcomes

2.5

The primary study outcome is the cardiorespiratory fitness value, assessed at the beginning of the intervention and after a 12-week and 1-year follow-up period. The study's secondary intervention outcome is the health-related quality of life, anxiety and depression, body composition, the incidence of treatment-emergent adverse events assessed by 5-grade scale, training adherence (number of compliant participants, average exercise time, overall completition rate). Assessment of the cardiorespiratory fitness, health-related quality of life, depression, anxiety, and body composition will be evaluated at the beginning of the study (T0), after 12-weeks (T1), and after 1-year period (T2).

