If we show that HIIT significantly increases cardiorespiratory parameters, it means better results in the CHD population, leading to a decrease in mortality and hospital readmission reduction.^[6]^

Secondary analyzes may suggest that even shorter CR programs may lead to better long-term results. If we can prove that telerehabilitation is a safe intervention, it can mean a step towards implementing this method into standard preventive care. The importance of safety and control of home CR remains a challenge, especially as the population of CHD patients ages and the number of comorbidities and the severity of cardiovascular risk increase.^[34]^ The telerehabilitation approach has the potential to positively influence barriers and improve the overall use of the CR program.

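### Adverse events are captured through training datasheets and unsolicited reports, with no window set for the incidence outcome, so events in patients who stop training may be under-recorded

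*Protocol article*

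**What the plan says.** Section 2.5 (Outcomes) lists among the secondary outcomes "the incidence of treatment-emergent adverse events assessed by 5-grade scale". It attaches no time window. The sentence there that begins "Assessment of the cardiorespiratory fitness, health-related quality of life, depression, anxiety, and body composition will be evaluated at the beginning of the study (T0" and continues to T1 and T2 does not include adverse events.

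Section 2.8 (Training adherence and adverse events) names two routes of capture:

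- A platform record: "incidence of the adverse events will be recorded in the exercise datasheets from the telemonitoring platform for both groups during the 12-weeks training program".
- Reports that the patient starts: participants will be "encouraged to use the contact details for reporting the incidence of treatment-emergent adverse events at any time throughout the study period". By section 2.1 the study period ends at 12 months (T2).

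Section 2.3 (Training program, text after Figure 2) has the coach "provide remote guidance (motivation, feedback on the frequency, duration, and intensity of training) via a preferred phone call once a week". Adverse events are not part of that stated content. The same section has patients uploading their own training data to the web application and ends telemonitored sessions after 3 months, with advice to keep exercising.

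The Discussion (section 3) begins one sentence "If we can prove that telerehabilitation is a safe intervention" and goes on to adoption into standard care.

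**The concern.** A datasheet exists only if a session took place and was uploaded. A patient who stops training because of an event leaves no datasheet from that point on, so the platform record is weakest where a safety outcome needs it most. The remaining route relies on the patient choosing to report.

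Both weaknesses can act unequally on the two arms. Section 2.2 says that participants cannot be blinded, so readiness to report may depend on the allocated training. The Abstract and Discussion also expect HIIT to be harder to carry out at home than in a centre, so adherence may differ. The recorded HIIT versus MICT contrast in events would then partly reflect who kept uploading and who chose to call.

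At stake are the credibility of a secondary safety outcome and of what the report can say about the safety of home HIIT. Under-recorded events cannot be reliably recovered at analysis.

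**Working it through.** **1. What each stated route can capture**

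- Weeks 1 to 12, patient training and uploading: platform datasheet plus own report.
- Weeks 1 to 12, patient no longer training or uploading: own report only.
- Week 13 to month 12, all patients: own report only, because telemonitored sessions have ended.

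Section 2.8 grades events from 1 to 5, and grade 5 is death. A training datasheet does not show a death, and the patient can no longer make contact, so the top of the scale needs a route other than the two named.

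**2. What the outcome window would have to be**

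Section 2.5 gives none. If incidence is counted over 12 weeks, the later reports fall outside it. If it is counted over 12 months, it adds a period with two routes to a longer period with one. Either could be reported, but the article does not say which.

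**3. What differential capture would do (illustration; the shares are assumptions)**

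Let *s* be the share of patients with an event whose event goes unrecorded. Recorded risk = true risk × (1 − *s*). With equal true risks, the recorded HIIT/MICT ratio is (1 − *s*_HIIT) / (1 − *s*_MICT):

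- 10% lost in both arms: 0.90/0.90 = 1.00
- 20% HIIT, 10% MICT: 0.80/0.90 = 0.89
- 30% HIIT, 10% MICT: 0.70/0.90 = 0.78
- 10% HIIT, 30% MICT: 0.90/0.70 = 1.29

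Equal loss lowers both incidences but leaves the ratio alone. Unequal loss moves the ratio in either direction.

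**4. What the trial could show about safety with perfect capture**

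The article states no sample size, expected rate or test for adverse events. The available denominators are 38 per arm and 76 in total (section 2.12), set for cardiorespiratory fitness. The exact upper limit after zero events in *n* patients is 1 − (α/2)^(1/*n*) for a two-sided interval and 1 − α^(1/*n*) for a one-sided one, with α = 0.05:

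- *n* = 38: two-sided 1 − 0.025^(1/38) = 9.3%; one-sided 1 − 0.05^(1/38) = 7.6%
- *n* = 76: two-sided 1 − 0.025^(1/76) = 4.7%; one-sided 1 − 0.05^(1/76) = 3.9%

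These limits assume that every event is captured. They bear only on the word prove in the Discussion. They do not measure under-recording, and better questioning would not change them.

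**The case against.** The strongest reply is that loss of events is possible but not shown. The contact route is open to everyone for the whole study, including patients who stop training. The Abstract says that patients give feedback at the weekly call. A coach who sees no uploads is still due to phone. There are visits at T1 and T2, and a cardiologist attends the exercise test. A journal article may also leave the call script and the adverse-event form to the full protocol. Most of this stands, and it rules out several stronger readings that a reader might infer:

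- **That events in patients who stop training are missed.** The text supports a risk of under-recording, not a certain loss.
- **That the two periods in section 2.8 contradict each other.** They belong to two routes: a datasheet record during the programme and open reporting throughout. A 12-week datasheet period agrees with telemonitoring ending at 3 months.
- **That recording covers only 12 weeks of the year.** This overlooks the second route.
- **That the trial plans a safety conclusion which then fails.** The Discussion sentence is conditional, and there is no safety hypothesis, margin or test.

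The reply does not remove the point itself. The finding is not that a call script is absent. Section 2.8 states how events will be recorded, and that method, followed as written, ties capture to uploading or to patient initiative. The calls and visits are available, but the article gives them no part in recording events. The missing window in section 2.5 and the word prove also remain.

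**Conclusion.** The concern holds as a risk of under-ascertainment and an outcome window left open. Patients who stop training or uploading are covered only by their own unsolicited reports, and after week 12 so is everyone. The loss could differ between unblinded arms if adherence differs. Its size and direction cannot be derived from the article, which gives no stopping, adherence or capture rates; the ratios of 0.78 to 1.29 above only illustrate assumed losses of 10% to 30%.

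The safety wording is a separate and smaller matter. Because both arms receive telerehabilitation, no comparison in this trial can show that telerehabilitation as such is safe. Even with full capture and no events, risks up to 9.3% in one arm or 4.7% overall would remain compatible with the data (two-sided 95%).

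The change should be made: it is cheap now and hard to repair later. It does not affect the primary outcome.

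**What to change.** - **Sections 2.3 and 2.8:** ask the same fixed adverse-event question in both arms at each weekly call, whether or not training was uploaded, and again at the T1 and T2 visits. Keep the datasheets and open reporting as additional sources. At the visits, have someone other than the blinded examiner ask, since the answer may reveal the allocation.
- **Section 2.5:** state one window for the incidence outcome, the same in both arms, or report the first 12 weeks and the later period separately.
- **Reporting:** give patients with at least one event over all randomised, by arm, with exact 95% confidence intervals.
- **Discussion:** replace the clause "If we can prove that telerehabilitation is a safe intervention" with an aim to estimate event incidence under home HIIT versus home MICT.

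The cost is one scripted question in contacts already planned, plus a few sentences of rewording. The small downside is that recorded event counts will be higher than under passive reporting.

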### Anxiety and depression

2.9

The hospital anxiety and depression scale will be assessed in the study period from baseline to 12 weeks and 1 year. The questionnaire comprises 7 questions for anxiety and 7 questions for depression. Each item in the questionnaire is scored from 0 to 3 and which means every person can score between 0 and 21 for either anxiety or depression. The hospital anxiety and depression scale is a validated measure licensed to CR to assess anxiety and depression symptoms and is recommended for use with patients with CHD.^[24]^

### Body composition

2.10

Anthropometrics of the study patients will be assessed at all three-time points (T0–T3). Bodyweight (accuracy = 0.1 kg) and body composition, including total muscle mass, fat mass, and body water, will be measured by bioelectrical impedance analysis from analyzer InBody 370S (BridgePower Corp, Suwon, Korea). Bioelectrical impedance analysis is a non-invasive rapid examination for evaluating body composition.^[25,26]^

Body mass index will be calculated through a simple calculation using a patient's height and weight. The formula is Body mass index = kg / m2, where kg is a patient's weight in kilograms, and m2 is the patient's height in meters squared.

### Statistics

2.11

The Shapiro-Wilk test will be used to evaluate normality. Comparisons between subjects will be made using the Student *t* test and Mann–Whitney *U* test. The 2-tailed Fisher exact test will test differences in proportions. Data will be summarized as a mean ± standard deviation; *P* values < .05 will be considered statistically significant. Statistica software 12.0 (TIBCO Software Inc, Palo Alto) will be used for statistical analysis.

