**Methods::**

This study is designed as a monocentral randomized controlled trial at University Hospital Brno in the Czech Republic. After the coronary heart event, the suitable patients will be randomized (1:1 ratio) and separated into 2 groups: the experimental HIIT group and the control MICT group. Both groups undergo a 12-week telerehabilitation with a 1-year follow-up period. Study participants will be telemonitored during physical training in their home environment via a heart rate monitor and a web platform. Once a week, the patients will give their feedback and motivation by a telephone call.

The primary outcome observed will be the effect of intervention expressed by changes in cardiorespiratory fitness. Secondary outcomes will be the health-related quality of life, anxiety, training adherence, body composition, safety, and satisfaction.

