### Power analysis

2.12

The group size is based on an anticipated increase of cardiorespiratory fitness 2.8 mL/kg/min with a standard deviation of 4.3 mL/kg/min from the previous study.^[16]^ Seventy-six participants will need to be included in the study to achieve 80% statistical power at 5% statistical significance. The drop-out rate in follow-up at 12 week and follow-up is taken into account, that is, 38 participants need to be randomized to the experimental and control arm of the study.

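### The arms are to be compared by unadjusted two-sample tests although baseline peak VO2 is measured, and their power depends on whether the primary outcome is a value or a change; ANCOVA on baseline resolves this almost free

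*Protocol article*

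**What the plan says.** - **Analysis (section 2.11, Statistics).** "The Shapiro-Wilk test will be used to evaluate normality". Then: "Comparisons between subjects will be made using the Student" t test and the Mann-Whitney U test. No covariate is named, and no rule says when each test applies.
- **Primary outcome, abstract (Methods).** It is "the effect of intervention expressed by changes in cardiorespiratory fitness".
- **Primary outcome, section 2.5 (Outcomes).** "The primary study outcome is the cardiorespiratory fitness value, assessed at the beginning of the intervention and after a 12-week and 1-year follow-up period". A baseline measurement is therefore planned, and no single time point is marked as primary.
- **Sample size (section 2.12, Power analysis).** It rests on an "anticipated increase of cardiorespiratory fitness 2.8 mL/kg/min" "with a standard deviation of 4.3 mL/kg/min from the previous study". The text does not say whether that SD describes the attained value or the change from baseline. The result is 76 patients, 38 per arm, for 80% power at 5% significance.

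**The concern.** A patient's peak oxygen uptake before training is usually a strong predictor of the same measurement afterwards. A plan that measures it and then compares the arms without it leaves precision unused.

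The two wordings of the primary outcome add a second problem. Attained values and changes generally have different variances, so the same 76 patients can give quite different power depending on which is tested. The single planning SD cannot be matched to either with certainty.

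The test is also not fixed. Shapiro-Wilk stands next to one parametric and one rank test, and the natural reading is that its result guides the choice. Mann-Whitney does not test the mean difference in mL/kg/min on which section 2.12 is built, so the quantity behind the primary P value could depend on the data.

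At stake are the power of the primary comparison and a clear statement of what it estimates.

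**Working it through.** **Inputs from the article.** Difference 2.8 and SD 4.3 mL/kg/min, 80% power, 5% significance, 38 per arm (section 2.12); 1:1 allocation (section 2.2).

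**Assumptions, not in the article.** Two-sided test; equal variance at T0 and follow-up; correlation r between them from 0.5 to 0.9; no losses.

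**Step 1: the plan's own figure.** n per arm = 2 × (1.960 + 0.842)² × (4.3/2.8)² = 37.02, rounded up to 38, so 76 in total. A one-sided calculation gives 30 per arm (60 in total) and does not match. The noncentral t distribution gives 80.0% power at 38 per arm. The stated size is therefore that of an unadjusted, two-sided, two-sample comparison.

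**Step 2: link between the SDs.**
- SD(change) = SD(value) × √(2(1 − r))
- ANCOVA residual SD = SD(value) × √(1 − r²) = SD(change) × √((1 + r)/2)

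**Step 3: power for a difference of 2.8 with 38 per arm** (noncentral t).

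Case A, 4.3 is the SD of the change. A t test on change has 80% throughout.

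| r | SD of value | t test on value | ANCOVA residual SD | ANCOVA |
|---|---|---|---|---|
| 0.5 | 4.30 | 80% | 3.72 | 90% |
| 0.7 | 5.55 | 58% | 3.96 | 86% |
| 0.8 | 6.80 | 43% | 4.08 | 84% |
| 0.9 | 9.62 | 24% | 4.19 | 82% |

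Example at r = 0.7: SD of value = 4.3/√0.6 = 5.55; ANCOVA residual SD = 4.3 × √0.85 = 3.96.

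Case B, 4.3 is the SD of the value. A t test on values has 80% throughout.

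| r | SD of change | t test on change | ANCOVA residual SD | ANCOVA |
|---|---|---|---|---|
| 0.5 | 4.30 | 80% | 3.72 | 90% |
| 0.7 | 3.33 | 95% | 3.07 | 98% |
| 0.8 | 2.72 | 99% | 2.58 | over 99% |
| 0.9 | 1.92 | over 99% | 1.87 | over 99% |

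**Step 4: value or change under ANCOVA.** Write the model as follow-up = a + b × arm + c × baseline + error. Subtracting baseline from both sides gives change = a + b × arm + (c − 1) × baseline + error. The arm coefficient b and its standard error are unchanged, so the choice of wording no longer affects the treatment result.

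**Step 5: a normality test as selector.** If Shapiro-Wilk is applied at 5% in each arm, exactly normal data would fail in at least one arm with probability 1 − 0.95² = 9.75%. A simulation with 34 per arm agreed (9.4% to 10.1%) and put the type I error of the two-stage procedure at 5.1%. The consequence is an uncertain estimand, not an inflated error rate.

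**The case against.** **The stated tests are not wrong.** In a randomised trial an unadjusted t test is valid on values or on changes, and chance baseline imbalance is already covered by its error rate. This stands. A reader might infer bias or a false-positive problem; nothing in the article supports that. The issue is efficiency and an endpoint worded two ways.

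**The large power loss needs a particular combination.** Power of 43% or 24% arises only if 4.3 is the SD of change, attained values are what is tested, and r is high. The abstract and the word increase in section 2.12 lean towards change, and section 2.5 may simply be naming the variable and its visits. This also stands. Against a t test on change in case A, ANCOVA gains about 10 points at r = 0.5 and only 2 at r = 0.9. At r = 0.5 value and change have equal power. A reader should not take 43% as the trial's power.

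**The normality gate is inferred.** Section 2.11 does not say that Shapiro-Wilk selects the test, and the paragraph covers every outcome, including bounded questionnaire scores for which a rank test is natural. So the gate is the likely reading, not a stated rule.

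**A condensed article may leave modelling to a fuller plan.** That is fair for the analysis set and for longitudinal modelling, and their absence is not criticised here. But the article does positively name two-sample tests and does give two wordings of the outcome.

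**Follow-up visits.** A reader might infer that testing each visit separately discards 12-week data from patients who miss the 1-year visit. It does not: a T1 test uses every T1 observation.

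**Conclusion.** The point holds as a matter of efficiency and specification. Section 2.11 fixes unadjusted comparisons although a baseline is measured, and the outcome wording leaves open which comparison is made.

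With 38 per arm, ANCOVA has at least 82% power over r = 0.5 to 0.9 under either meaning of 4.3. The unadjusted test ranges from 24% to over 99% across the same combinations. The gain over a change-score test is modest (about 2 to 10 points in case A, 10 points or less in case B). The gain over attained values is 10 to 58 points in case A and 10 to about 20 in case B.

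These sizes rest on an assumed correlation, equal variances and no losses. The direction does not depend on the exact r: over this range ANCOVA is never less powerful than either unadjusted test.

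ANCOVA does not settle whether 12 weeks or 1 year is primary. Section 2.5 lists both, and a reader should not infer from the article that either has been chosen.

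**What to change.** - Make the primary analysis an ANCOVA of follow-up peak VO2 on arm with T0 peak VO2 as covariate, and report the adjusted mean difference with its 95% confidence interval.
- Name the primary time point, 12 weeks or 1 year. This is the sponsor's decision.
- Use one wording of the primary outcome in the abstract and section 2.5, and state in section 2.12 whether 4.3 is the SD of the value or of the change.
- State that no normality test selects the primary test, and keep Mann-Whitney as a sensitivity analysis.
- A mixed model over T1 and T2 with baseline as covariate is an acceptable alternative. It is not equivalent to a single-visit ANCOVA when visits are missing, because it keeps patients with only one follow-up visit and relies on a missing-at-random assumption.

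Cost: one degree of freedom, one rewritten paragraph in section 2.11 and small wording changes elsewhere. No new data or extra patients are needed.

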**Discussion::**

The HIIT is widely researched predominantly in a center-based supervised form. Our study differs from others by the use of telemedicine and smart technologies in home-based settings. Previous home-based cardiac telerehabilitation studies have focused primarily on MICT, which has demonstrated feasibility, and results have shown similar improvements as center-based CR. There is a presumption that HIIT may be superior to MICT. However, it can be complicated to self-dose the method in the home environment. Investigators expect that HIIT research will provide insight into the possibilities of telemedicine feasibility, effect, and limitations of coronary heart disease patients’ use at low to moderate cardiovascular risk.

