### Population and randomization

2.2

Participants suitable for this study will be the patients of UH Brno older than 18 years, diagnosed with CHD (angina pectoris or myocardial infraction in last eight weeks), with low or medium cardiovascular risk status (without residual coronary stenosis, value of left ventricular ejection fraction more than 40%).^[17]^ After heart revascularization, the participants will be referred to the II. phase of CR with the recommended pharmacotherapy. Further eligibility criteria will be clinically stable state, ability to perform physical training and cardiopulmonary exercise test (CPET), ability to understand and write in the Czech language, internet connection at home, and literacy with information and communication technology. The participants’ recruitment and allocation will be monitored by the study cardiologist, physiotherapist, or an assistant in UH Brno, Czech Republic.

The exclusion study criteria are patients hospitalized with CHD in the previous 6 weeks, severe psychological or cognitive disorders, serious training limitations besides CHD, participation in another training program under supervision, and contraindications for CPET.

Participants will be randomized (in 1:1 ratio) into the experimental HIIT group and control the MICT group via computer sequence generated by the study statistician. The treatment allocation will be hidden until the completion of the baseline of the initial examinations in sequentially numbered, sealed, opaque envelopes. The study participants cannot be blinded by treatment allocation, but researchers who perform line examinations will be blinded by treatment allocation.

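### The two-sample tests named for a fitness outcome measured three times discard the 12-week values of patients lost before 1 year, which costs precision and can bias the 1-year comparison

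*Protocol article*

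**What the plan says.** - Section 2.5 (Outcomes) makes cardiorespiratory fitness the primary outcome, "assessed at the beginning of the intervention and after a 12-week and 1-year follow-up period". Section 2.1 labels these times T0, T1 and T2.
- Section 2.11 (Statistics) gives the between-arm method for continuous data: "Comparisons between subjects will be made using the Student" t test and the Mann-Whitney U test, after a Shapiro-Wilk check of normality. Fisher's exact test is for proportions. No method that uses more than one visit is named.
- Section 2.12 (Power analysis) expects loss at both follow-ups: "The drop-out rate in follow-up at 12 week and follow-up is taken into account". It gives no rate, overall or by arm.
- The Discussion part of the Abstract says of home HIIT that "it can be complicated to self-dose the method in the home environment". This concerns control of training intensity, not retention.

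**The concern.** A two-sample test takes one number per patient. At 1 year that number is the T2 value or the change from T0 to T2. A patient with exercise tests at T0 and T1 but none at T2 has no such number and leaves the comparison, although the 12-week result is informative about the missing one.

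Two things are at stake. The first is precision, since observed data are thrown away. The second is bias. If patients with a small 12-week gain are less likely to return at 1 year, and this happens more in one arm or only in one arm, the remaining patients are no longer comparable. If that arm is HIIT, the error favours the superiority claim that the trial sets out to make; if it is MICT, the error runs the other way. Adjusting for T0 alone would not cure this, because it does not bring in the 12-week value of a patient missing at 1 year.

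**Working it through.** **Inputs from the article.** Difference: "anticipated increase of cardiorespiratory fitness 2.8 mL/kg/min", read as the difference between arms. SD: 4.3 mL/kg/min. Target: "achieve 80% statistical power at 5% statistical significance", taken as two-sided. Allocation 1:1, 38 per arm.

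**Inputs assumed, because the article has none.** Loss rates; the link between loss and 12-week gain; SD of change 4.3 at both visits; correlation r between 12-week and 1-year change of 0.5 to 0.8.

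**1. The plan's own figure.** n per arm = 2 × (1.960 + 0.842)² × (4.3/2.8)² = 2 × 7.85 × 2.358 = 37.02, rounded up to 38, or 76 in total. The noncentral-t solution is 38.006 per arm. So 76 is reproduced with no drop-out at all. With 38 per arm randomised and only observed cases analysed, t-test power is 0.800 at no loss, 0.756 at 10%, 0.704 at 20% and 0.644 at 30%. The conflict with the statement that drop-out is allowed for is a separate point. It matters here only because the design has no precision to spare.

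**2. Precision.** Let a fraction p be lost at random after T1. In large samples the variance of the 1-year contrast is proportional to 1/(1 − p) for completers only, and to r² + (1 − r²)/(1 − p) for a likelihood analysis that also uses T1. The ratio of the second to the first is 1 − p·r². With p = 0.20:
- r = 0.5: 1 − 0.20 × 0.25 = 0.950, a 5% saving.
- r = 0.8: 1 − 0.20 × 0.64 = 0.872, a 13% saving.

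Simulation at 38 per arm gave 5% to 12%.

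**3. Bias, simple form.** If drop-outs do worse than completers by D in both arms, the completer comparison is off by (d_HIIT − d_MICT) × D, where d is the fraction lost.
- 20% versus 10%, D from 1 to 4.3: 0.10 × 1 = +0.10 to 0.10 × 4.3 = +0.43.
- 30% versus 10%: 0.20 × 1 = +0.20 to 0.20 × 4.3 = +0.86.
- Equal loss: 0.

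**4. Bias, loss after T1 that depends on 12-week gain.** Simulation at 38 per arm with no true difference. Where loss is response-related, its odds are 3.3 times higher per SD lower 12-week gain. Ranges run over r = 0.5 to 0.8.

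| Loss, HIIT v MICT | Response-related in | Bias of 1-year t test (mL/kg/min) | False-positive rate (nominal 5%) |
|---|---|---|---|
| 20% v 20% | both arms, same mechanism | about 0 | not tabulated |
| 22% v 20% | both arms, same mechanism | +0.04 to +0.06 | about 4% to 5% |
| 31% v 15% | both arms, same mechanism | +0.33 to +0.53 | about 5.5% to 7.6% |
| 22% v 20% | HIIT only, MICT random | +0.46 to +0.71 | about 7% to 10.5% |
| 31% v 15% | HIIT only, MICT random | +0.62 to +1.00 | about 9% to 15% |

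The biases are from one set of runs. The false-positive rates span repeated runs of the same settings, which agreed closely on bias. Loss that is unequal but random gives no bias.

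Against the planned 2.8, +0.33 to +0.53 is 12% to 19% (0.33/2.8 and 0.53/2.8), and +1.00 is 36%. A likelihood-based analysis of the same HIIT-only data had bias within ±0.03. That is partly by construction, since loss was generated to depend only on the observed T1 value.

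**The case against.** The strongest reply is that this rests on silence. Section 2.11 is five sentences in a journal article. It does not say that the analysis is visit by visit or that untested patients are excluded, and analysis sets and missing-data handling are commonly left to a fuller document that is not shown. That stands as far as it goes: a reader might infer that the plan fixes a completers-only analysis, and the article does not say so. What remains is the method that section 2.11 does name. A two-sample test at 1 year has no place for a 12-week value. Imputation could be added around it elsewhere, but a repeated-measures model would replace it, so the wording would have to change.

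A reader might also infer that HIIT, being harder to do at home, will lose its poor responders and that the 1-year result will therefore be biased towards HIIT. The article does not support this. It gives no drop-out rate, does not link loss to response, and does not predict higher loss in HIIT. Its remarks on difficulty concern accuracy of intensity. HIIT sessions are also shorter (33 versus 41 minutes, section 2.3), which could help retention. Telemonitored training ends at 3 months, so difficulty in self-dosing during the programme is weak evidence about loss in the following nine months.

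The larger biases do depend on letting HIIT loss alone follow response. With one mechanism in both arms and similar loss, the bias nearly vanishes. That objection stands in full and sets the wording of the conclusion.

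**Conclusion.** The point holds in conditional form. The tests named in section 2.11 do not by themselves use the data the trial will have on patients lost between 12 weeks and 1 year, although section 2.12 expects such losses. The loss of precision follows whenever the two changes are correlated, and is modest: about 5% to 12% in variance at an assumed equal random 20% loss. Bias is possible but not established. It needs loss that is related to response and differs between arms in rate or mechanism. Under the assumed scenarios it runs from about 0, through +0.3 to +0.5 mL/kg/min (31% versus 15%, common mechanism), to about +1.0 (31% versus 15%, only HIIT loss response-related), against a planned difference of 2.8. The direction shown is for heavier or more selective loss in HIIT and reverses if MICT is the arm affected. The article supports none of these rates, so the comparison can be biased; it cannot be said that it will be. The change is worth making because it is cheap and improves precision even where there is no bias.

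**What to change.** In section 2.11, make the primary analysis of peak oxygen uptake one likelihood-based repeated-measures model:
- T0, T1 and T2 values as responses, with baseline means constrained equal across arms, arm-by-visit effects and an unstructured covariance;
- all randomised patients, in their allocated arm;
- the 12-week and 1-year contrasts both taken from this model.

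T0 must be among the responses. A model of T1 and T2 alone takes nothing from patients lost before 12 weeks and so would not include everyone randomised. Section 2.2 keeps allocation concealed until the baseline examinations are complete, so every randomised patient should have a T0 value.

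Keep the two-sample test as a sensitivity analysis. Add one shifted-value check, in which missing T2 values are set lower than the model predicts, to see how large a shift would change the conclusion.

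Cost: analysis wording and a few lines of code, with no new patients or visits. Downside: the model assumes that loss is explained by observed values. The shifted-value check addresses that assumption but cannot prove it.
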